## Abstract

**Introduction:**

Only 30%–50% of people referred to clinics during community-based eye screening are able to access care in Botswana, India, Kenya and Nepal. The access rate is even lower for certain population groups. This platform trial aims to test multiple, iterative, low-risk public health interventions and simple service modifications with a series of individual randomised controlled trials (RCT) conducted in each country, with the aim of increasing the proportion of people attending.

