**Figure 1 F1:**
[figure not shown]
Three example individual trials that test new interventions against the status quo (grey boxes) as part of an overall platform trial.

Addressing inequitable service outcomes is likely to require multiple different modifications in the context of continuous improvement. Early data from Botswana suggest that approximately one-tenth of school children have an unmet eye health need but less than a third are able to access community eye clinics to receive care. Data from Kenya suggests that only a third of younger adults identified with an eye need are able to access care.

In each setting where Peek eye screening programmes run, we intend to engage with representatives from groups that are facing the highest barriers to accessing care to explore their perceptions of the types of interventions and service modifications that could improve access. Our platform trial will be used to test the interventions suggested by these left behind groups.

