### Discontinuing or modifying interventions

Arms will be discontinued (or modified to remove the risk) if there is evidence that they are harming exposed individuals. We note that only low/negligible-risk service modifications will be tested. Risk will be assessed at the intervention selection stage by a group of researchers, programme managers and lay representatives. Interventions that are deemed to be appropriate will also be independently reviewed by independent ethics committees in each setting before they are implemented in the platform trial.

There are no *a priori* strategies to improve adherence as we are not prespecifying the interventions.

As our trials will be embedded within routine service delivery, we cannot exclude the possibility that other initiatives will be introduced by local teams before, during or after individual trials. We will report all programmatic changes that take place during individual trials that could bias our findings.

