### Data collection

#### Data collection methods

As stated above, outcome assessment (attendance at clinic) will be recorded when participants check-in at the clinic on their appointed date. Each participant’s attendance status will be recorded on their central record.

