#### Retention

There are no plans to promote participant retention and complete follow-up.

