### AE reporting and harms

An AE is defined as any untoward medical occurrence in a patient or study participant. All AEs will be reported. Depending on the nature of the event, the reporting procedures below will be followed. Any questions concerning AE reporting will be directed to the study coordination centre in the first instance. The flowchart below has been provided to aid the reporting of AEs.

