#### Serious AEs

Serious AEs (SAEs) will be reported to the PI and study coordination centre within 24 hours of the local site being made aware of the event (online supplemental figure S3). The PI will report the event to the data safety monitoring committee within 48 hours and include it in the study safety report.

An SAE form will be completed and submitted to the PI and study coordination centre with details of the nature of event, date of onset, severity, corrective therapies given, outcome and causality. All SAEs whether expected, suspected or unexpected will be reported to regulatory bodies and the trial DSMB within 48 hours of occurrence. The responsible investigator will assign the causality of the event. All investigators will be informed of all SAEs occurring throughout the study. If awaiting further details, a follow-up SAE report should be submitted promptly upon receipt of any outstanding information.

Any events relating to a pre-existing condition or any planned hospitalisations for elective treatment of a pre-existing condition will not need to be reported as SAEs.

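### The promise to report all adverse events has no ascertainment to match it: check-in is the only planned contact common to all trials, 50–70% of referred people do not reach it, and the two serious-event clocks conflict

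*Protocol article*

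**What the plan says.** Under AE reporting and harms the definition is broad: "An AE is defined as any untoward medical occurrence in a patient or study participant". The commitment that follows has no limit: "All AEs will be reported". The two subsections on non-serious and serious events say to whom a known event is passed and how fast. They do not say how, when or over what period events are looked for.

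Under Retention: "There are no plans to promote participant retention and complete follow-up". Under Data collection methods, "outcome assessment (attendance at clinic) will be recorded when participants check-in at the clinic on their appointed date". The Consent section gives participants the research managers' contact details. The Participant timeline mentions SMS reminders in most programmes, but only as outgoing messages up to the day before the appointment.

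On how many people reach the clinic, the Abstract says: "Only 30%–50% of people referred to clinics during community-based eye screening are able to access care". For school children in Botswana the Introduction says "less than a third are able to access community eye clinics to receive care".

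Under Serious AEs, the report to the investigator and coordination centre is due "within 24 hours of the local site being made aware of the event". The same section also requires serious events to reach regulators and the safety board within 48 hours counted from when the event happens.

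Harm data have a use. Under Discontinuing or modifying interventions: "Arms will be discontinued (or modified to remove the risk) if there is evidence that they are harming exposed individuals". The safety board in each country also advises on continuing or stopping on safety grounds.

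**The concern.** A promise covering every untoward occurrence in every participant needs a way of learning about events in people who never come to the clinic. The article describes only passive routes for them. The commitment therefore cannot be shown to have been met.

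The second issue is comparability. Attendance happens after randomisation and is what the arms are meant to change. If events come to light mainly at check-in or triage, an arm that raises attendance will show more events at the same true risk, and an arm that lowers it will show fewer. A board asked whether an arm is harming people would be reading counts that partly reflect the primary outcome. Because the definition is not limited to related events, ordinary background illness is counted too, and it is open to the same distortion.

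**Working it through.** **Inputs from the protocol.** Access after referral is 30%–50% (Abstract). I treat this as attendance, since the protocol uses attendance as its proxy for access. The attendance effects simulated run from 0 to 5 points with 50% in the control arm (Sample size, operating characteristics).

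**Inputs assumed.** The protocol gives no adverse-event rate and no detection rate, so there is no figure of its own to reproduce. Detection in non-attenders relative to attenders, *s*, is varied over 0, 0.25, 0.5 and 1. True event risk is taken as equal in attenders and non-attenders unless stated.

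**Step 1: people who do not reach check-in.** 1 − 0.50 = 50%; 1 − 0.30 = 70%.

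**Step 2: share of events not seen.** With full detection in attenders, attendance *p* and equal risk, the share is (1 − *p*)(1 − *s*).

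| *s* | *p* = 0.30 | *p* = 0.50 |
|---|---|---|
| 0 | 70% | 50% |
| 0.25 | 0.70 × 0.75 = 52.5% | 0.50 × 0.75 = 37.5% |
| 0.5 | 0.70 × 0.5 = 35% | 0.50 × 0.5 = 25% |

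With *s* = 0 and risk in non-attenders *RR* times that in attenders, the share is (1 − *p*)*RR* / [*p* + (1 − *p*)*RR*]. For *RR* = 0.5 this is 0.35/0.65 = 54% at 30% attendance and 0.25/0.75 = 33% at 50%. For *RR* = 2 it is 1.4/1.7 = 82% and 1.0/1.5 = 67%.

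**Step 3: observed ratio between arms when the true risk is equal.** Ratio = [*p*T + (1 − *p*T)*s*] / [*p*C + (1 − *p*C)*s*], where T is the arm with better attendance and C the control.

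| *s* | 30% to 35% | 50% to 55% |
|---|---|---|
| 0 | 0.35/0.30 = 1.17 | 0.55/0.50 = 1.10 |
| 0.25 | 0.5125/0.475 = 1.08 | 0.6625/0.625 = 1.06 |
| 0.5 | 0.675/0.65 = 1.04 | 0.775/0.75 = 1.03 |
| 1 | 1.00 | 1.00 |

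For a 1-point gain with *s* = 0 the ratios are 0.31/0.30 = 1.03 and 0.51/0.50 = 1.02. Equal ascertainment in attenders and non-attenders (*s* = 1) removes the distortion whatever the attendance difference.

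**Step 4: the two serious-event clocks.** Where triage is at a central clinic, the Participant timeline puts the appointment commonly 1–2 weeks after screening. An event soon after referral that is first mentioned at check-in can meet the awareness-based clock. It cannot meet a 48-hour clock that started when it occurred. This holds for attenders as well as non-attenders.

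**The case against.** The strongest reply is that the section is about reporting, not detection: known events are passed on, and the first serious-event clock starts at awareness. On that reading the promise already means events that staff hear of. The Retention sentence does not mention adverse events and does not bar safety follow-up. The article is condensed. The reporting flowchart, supplemental figure S3 and the data management plan are not shown, each individual trial has its own protocol, and each safety board sets its own charter. Non-attendance on the appointed date is also not the same as no contact: people may come on another day, screeners may be local primary care staff, and some arms involve chaperones or transport. Finally, only low- or negligible-risk changes are tested, and each event is logged with its relation to the intervention, so harm need not be judged on raw counts by arm.

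Much of this stands. It rules out saying that nobody follows up non-attenders, and it makes the link with attendance a conditional risk. Passive surveillance may be proportionate here. It does not make the unlimited wording accurate, and it does not reconcile the two clocks. Staff contact that exists only in some arms also makes detection less alike between arms.

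**Conclusion.** The point holds in a limited form. The unqualified promise does not fit a plan with no complete follow-up and a single common contact that 50–70% of referred people do not reach, and the serious-event section contains two incompatible clock starts. If events are noticed mainly at the clinic, counts by arm are inflated in the better-attended arm by about 10–17% at a 5-point gain with no detection in non-attenders. The figure is 6–8% with 25% relative detection and 3–4% with 50%.

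Three stronger readings are tempting and are not supported:

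- **Most events go unseen.** This needs similar risk and little self-report. At 50% attendance and no detection in non-attenders it is exactly half; with 25% self-report it is 37.5%.
- **Very large distortions.** Ratios such as 0.43/0.33 = 1.30 or 0.50/0.30 = 1.67 need attendance gains of 10 or 20 points, beyond the 0–5 points the protocol simulates.
- **A harmful arm would be adopted because it looks safe.** An arm that deters attendance would be losing on the outcome that drives the stopping rules.

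The protocol's error rates and power are unaffected. This is a change worth making, not a threat to the primary analysis.

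**What to change.** 1. Reconcile the Retention, AE reporting and Serious AEs sections. Limit the promise to adverse events that come to staff attention, and state the start of each serious-event clock so that the deadlines are compatible.
2. Add one field to the AE log for the detection route: found at check-in or triage, reported by the participant or family, or noticed by staff delivering the intervention.
3. Show the safety board events by allocated arm and route, with all persons allocated as the denominator. Label clinic-found events as attendance-dependent and not as an unbiased comparison between arms. Dividing them by attenders would not help, because that conditions on the post-randomisation outcome.
4. Where participants have a phone, have the software send the same automated message with the reporting contact to every participant in every arm, attender or not, after the outcome is recorded. The timing keeps it from influencing the endpoint.

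The cost is a wording change, one log field, a small SMS charge and more reports to log. The message misses people without a phone, so it reduces the dependence on attendance without removing it.

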#### Non-serious AEs

All non-serious AEs will be reported to the study coordination centre and recorded in a dedicated AE log within 72 hours. The entry must state the patient ID, date and time of AE, nature and relation to the intervention, if any. The AE should also be reported to the data and safety monitoring committee within 72 hours. AE logs will be stored on a secure, password-protected file on an LSHTM computer.

#### Serious AEs

Serious AEs (SAEs) will be reported to the PI and study coordination centre within 24 hours of the local site being made aware of the event (online supplemental figure S3). The PI will report the event to the data safety monitoring committee within 48 hours and include it in the study safety report.

An SAE form will be completed and submitted to the PI and study coordination centre with details of the nature of event, date of onset, severity, corrective therapies given, outcome and causality. All SAEs whether expected, suspected or unexpected will be reported to regulatory bodies and the trial DSMB within 48 hours of occurrence. The responsible investigator will assign the causality of the event. All investigators will be informed of all SAEs occurring throughout the study. If awaiting further details, a follow-up SAE report should be submitted promptly upon receipt of any outstanding information.

Any events relating to a pre-existing condition or any planned hospitalisations for elective treatment of a pre-existing condition will not need to be reported as SAEs.

### Limitations

We have chosen to use a prioritarian approach that focuses on left-behind population groups. This prevents a situation where we accept an intervention that improves mean attendance but is associated with a decline among left-behind groups. However, this approach does not hedge against the slope of inequality worsening. Unfortunately, using a proportionate approach where we assess whether gains in each group are proportionate to their initial need would risk attributing success to our intervention rather than the more likely detection of regression towards the mean.

Our estimate of the probability/proportion will be biased because, on average, the stopping rules will be triggered at a ‘local peak’. As such, we will be able to identify that, say, A is better than B, but the estimate of the attendance rate in A will be an overestimate.

We use attendance as a proxy for access. While this is the closest hard indicator available, the semantic implication of the term places responsibility on people rather than clinical systems or societal structures. We will counterbalance this in the language that we use to talk about barriers and in the framing of interventions in our individual study writeups. We also note that we focus on a proximal indicator that does not always correlate well with receipt of high-quality care or good clinical outcomes. We decided to focus on access for three main reasons; first, it aligns with the conceptual narrative of UHC^16^ and ‘leaving no one behind’, second, attendance data are already routinely collected and available for every single person who is referred, and third, internal Peek data suggest that the ‘fall off’ gap between those who are referred but do not attend is much larger than other gaps; for example, the proportion of those who attend but do not receive appropriate care, or the proportion of those who receive appropriate care but do not experience improved health outcomes.
